## Abstract

**Introduction:**

The concept of procrastination can be described as a conscious, yet irrational, postponement of important tasks or decisions—despite awareness that the delay may lead to negative consequences. Procrastination behaviours are common among university students and is often described as a failure of self-regulation, and the behaviour is associated with stress, symptoms of depression and anxiety, poorer academic performance and negative effects on overall health and well-being.

**Methods and analysis:**

A two-arm, parallel groups (1:1), single-blind randomised controlled trial will be conducted to assess the effectiveness of a brief digital procrastination intervention (Focus) among university students in Sweden. The intervention consists of a screening and feedback component based on Pure Procrastination Scale (PPS) score, allowing intervention participants to assess their current procrastination behaviours and receive behaviour change advice. Participants in the control group will be shown their total PPS score without any further feedback. Monte Carlo simulations (assuming a standardised effect of 0.35 Cohen’s d of the intervention on the primary outcome, to at least 80% of the time estimate a posterior probability of effect of at least 95%) indicated that data from 1000 participants are required for analysis, meaning that 2000 participants are required to be randomised when assuming a 50% attrition rate. The primary outcome will be procrastination behaviour measured at 2 months postrandomisation. Secondary outcomes will be anxiety and stress symptoms and lifestyle behaviours. Outcomes will be analysed using multilevel regression models estimated using Bayesian inference.

**Ethics and dissemination:**

The study was approved by the Swedish Ethical Review Authority on 2022-08-24 (dnr 2022-00353). Students will be asked to give informed consent before participation and after having been given information about the study. The results will be submitted for publication in open access, peer-reviewed journals.

**Trial registration number:**

ISRCTN13533793

STRENGTHS AND LIMITATIONS OF THIS STUDYPrevious research on procrastination has mainly focused on examining mechanisms behind the behaviour, and to a lesser extent on evaluating support that could be helpful in changing procrastination behaviours.The effectiveness of a novel brief digital intervention aiming to help college and university students change their procrastination behaviours will be evaluated.The trial design necessitates self-assessment of behaviours (self-monitoring), which itself may influence behaviours, leaving a potential risk of bias since the control group will be offered a chance to self-assess their behaviours.Attrition is a concern in digital intervention research and is anticipated to be a source of bias in the trial.

## Introduction

The concept of procrastination can be described as a conscious, yet irrational, postponement of important tasks or decisions—despite awareness that the delay may lead to negative consequences. To procrastinate has been defined by Steel as ‘to voluntarily delay an intended course of action despite expecting to be worse off for the delay’.^1^ For example, procrastinators tend to voluntarily keep busy with unrelated tasks instead of working to meet deadlines, leading to a short-term relief of undesired feelings associated with the prioritised task.

Procrastination is often described as a failure of self-regulation,^2^ and the behaviour is associated with stress, symptoms of depression and anxiety,^3 4^ poorer academic performance^5^ and negative effect on overall health and well-being.^6^ Previous research on procrastination has mainly focused on examining mechanisms behind the behaviour, for example, why people procrastinate and associations with personality traits such as impulsivity,^7^ and to a lesser extent on evaluating support that could be helpful in changing procrastination behaviours.^8^ Although procrastination of health behaviours is relatively unexplored in the literature,^9^ two examples of domain specific procrastination are ‘bedtime procrastination’ leading to insufficient sleep,^10^ and ‘exercise procrastination’ associated with lower overall physical activity even after controlling for intentions and general procrastination.^11^

Procrastination behaviours are common among university students and previous studies indicate that approximately 50% of students are likely to procrastinate their academic assignments or tasks.^12 13^ Also, in the general population, procrastination tends to be more common among younger adults aged 14–29 years.^4^ For many students, the transition to higher education involves more academic demands and lesser external control of things such as scheduled hours versus attention competition from social and digital activities. Students are responsible for their own study technique, and previously used strategies such as ‘last-minute-task performance’ might create a breeding ground for procrastination, which in turn might end up in negative health consequences.

The majority of scientifically evaluated procrastination support has been based on cognitive–behavioural therapy (CBT) treatment programmes, delivered both in face to face and digital settings, and both with and without additional support from a therapist.^14–19^ For example, a study by Rozental *et al*^14^ evaluated guided and unguided self-help using internet based CBT (iCBT)-treatment in the general population and showed a moderate effect on procrastination. Another study from Rozental *et al* compared iCBT with group therapy among university students with severe procrastination symptoms, and showed no statistically significant differences between groups after treatment.^15^ Eckert *et al*^16^ evaluated a 2-week unguided online intervention for university students to overcome procrastination, with and without additional text messages, which showed small to medium effects on procrastination.

Since procrastination is common among university students, and since it may lead to ill health and have a negative impact on academic performance, there is a need to develop and evaluate a scalable, brief digital procrastination intervention to reach a general student population in need of support.

### Aims and objectives

The primary aim of this study, which is called Focus, is to estimate the effects of a brief digital procrastination intervention on procrastination behaviours among university students in Sweden. Secondary aims include estimation of the effects of the intervention on anxiety and stress symptoms, as well as lifestyle behaviours. The study objectives are to:

Estimate the effects of a brief digital procrastination intervention on procrastination behaviours.Estimate the effects of a brief digital procrastination intervention on anxiety and stress symptoms.Estimate the effects of a brief digital procrastination intervention on alcohol consumption, intake of candy and snacks, sugary drinks, and physical activity.Investigate acceptability, perceived usefulness and general opinions of the intervention in terms of user experiences.

## Methods and analysis

A two-arm, parallel groups (1:1), single-blind randomised controlled trial (RCT) will be conducted to assess the effectiveness of a brief digital procrastination intervention targeting university students. This protocol includes relevant items from the Standard Protocol Items: Recommendations for Interventional Trials 2013 statement.^20^

### Study setting, recruitment and eligibility

The Focus study will be situated at colleges and universities in Sweden. Students at participating colleges and universities will be invited via email by their university student healthcare to participate in a study, in which they are asked to assess their procrastination. The email contains a hyperlink to a webpage presenting study information and informed consent materials (see online supplemental appendix A). Students who give informed consent will immediately be taken to a web-based questionnaire, which will collect baseline data and check for eligibility. Recruitment will begin in February 2023, and a final dataset will be available by the end of the semester of 2023.

10.1136/bmjopen-2023-072506.supp1Supplementary data

#### Eligibility criteria

Students completing the baseline questionnaire and scoring 20 points or more on the Pure Procrastination Scale (PPS) will be eligible for randomisation into the trial. There are no validated (or recommended) cut-offs of the PPS that indicate which individuals have no procrastination issues, rather, it is a continuous measure of procrastination. However, we did not want to include individuals who scored very low (no procrastination) since they would not be the target group in a future intervention implementation. However, we did want to be inclusive and therefore set the cut-off relatively low at 20 points (note the range of Perceived Stress Scale (PSS) is 12–60), excluding only those who report none or very little procrastination. As the survey will be conducted in Swedish, students not familiar with the Swedish language will be implicitly excluded. Excluded students will be given access to the digital intervention but will not be randomised into the study and not followed-up. After completing the questionnaire, eligible participants will be randomised to one of the two conditions: the Focus intervention (intervention group) or a non-treatment condition (control group). Figure 1 outlines the study design.

**Figure 1 F1:**
[figure not shown]
Study design flow chart. PPS, Pure Procrastination Scale.

### Interventions

#### Summary score and information (control group)

Participants allocated to the control group will be shown their total PPS score, with the minimum and maximum on the scale presented, and a recommendation to read more about procrastination at their local student healthcare website.

#### The Focus intervention (intervention group)

Participants allocated to the intervention group will be given the same information as the control group, but also be given access to the novel Focus intervention.

The Focus intervention is a digital procrastination intervention which is delivered online to students email and consists of a screening and feedback component, allowing participants to assess their current procrastination behaviours and receive behaviour change advice. The intervention is designed with inspiration from both previous research on procrastination treatment programmes using internet-based CBT (iCBT),^14 15^ and on the concept of brief alcohol interventions, which have been widely researched among university students in Sweden.^21^

The intervention was designed in iterative steps following the first stage (‘understanding the behaviour’) of the Behaviour Change Wheel (BCW) as a theoretical framework.^22 23^ Procrastination behaviour was understood by defining the problem in behavioural terms, specifying the target behaviour and identifying what needs to change in dialogue with professionals at the student healthcare centres during several multidisciplinary group meetings. Intervention content was also designed and developed in collaboration with the student healthcare centres.

The intervention starts with participants assessing their procrastination behaviour using the PPS questionnaire. Following the assessment, participants are given feedback on their current procrastination behaviours and personalised behaviour change advice. The items of the PPS have been found to load onto a 3-factor model^24^ where items 1–3 relate to decisional delay, items 4–8 to implemental delay and items 9–12 to timeliness and promptness delay. The feedback and advice given to participants as part of the digital intervention is therefore tailored in accordance with these latent constructs, allowing for prioritisation of advice based on the highest scoring construct.

The personalised advice component is based on the self-assessment and consists of graphical, written and interactive content. The feedback aims to enhance self-reflection and self-evaluation and aims to stimulate self-reinforcement on participants procrastination behaviour, in line with self-regulation theory.^25^
Figure 2 visualises screenshots of the intervention.

**Figure 2 F2:**
[figure not shown]
Screenshots of the intervention.

### Outcomes

The following outcome measures will be used. All study questionnaires can be found in online supplemental appendix B.

10.1136/bmjopen-2023-072506.supp2Supplementary data

#### Primary outcome measures

Procrastination behaviour.

#### Secondary outcome measures

Anxiety.Stress.Weekly alcohol consumption.Monthly frequency of heavy episodic drinking.Weekly consumption of candy and snacks.Weekly consumption of sugary drinks.Weekly moderate to vigorous physical activity (MVPA).

#### User evaluation

Perceived acceptability and usefulness of the intervention among users.

#### Primary and secondary outcome measures

Procrastination behaviour will be assessed by asking participants to complete the PPS 12-item PPS. Each item is scored on a five-point Likert scale with a higher score indicating greater difficulties with procrastination (12–60). The scale was originally developed by Steel^26^ and has been translated to Swedish and validated by Rozental *et al*,^27^ showing good internal consistency (Cronbach’s alpha=0.78).

Anxiety will be assessed using the validated seven item Generalised Anxiety Disorder scale,^28^ asking participants how often they, over the last 2 weeks, have been bothered by seven different anxiety related problems. Perceived stress will be assessed using the four item short form PSS, designed to measure experienced levels of stress,^29^ and considered a useful instrument for assessing stress perception levels in the general population.^30^

Procrastination behaviours are potentially a barrier for healthy lifestyle behaviours; thus we have added lifestyle behaviour outcome measures to explore this hypothesis. Weekly alcohol consumption will be assessed by asking participants the number of standard drinks of alcohol they consumed last week (short-term recall method). Frequency of heavy episodic drinking will be assessed by asking participants how many times they have consumed four or more standard drinks of alcohol on one occasion the past month. These two outcomes are both part of the proposed core outcome set for brief alcohol interventions.^31^

Diet and physical activity will be measured utilising a questionnaire based on the previously published questionnaire designed by the National Board of Health and Welfare in Sweden, and was further modified to also include portion sizes.^32^ Candy and snacks will be measured using a single question regarding number of servings consumed last week, and sugary drinks consumption will be measured by a question regarding the number of units (33 cl) of sugary drinks participants consumed the past week. Moderate and vigorous physical activity will be estimated by summing responses to two questions regarding the number of minutes spent on moderate and vigorous physical activity, respectively, during the past week.

At 2 months follow-up, participants allocated to the intervention group will be asked three questions about perceived acceptability and usefulness of the intervention.

### Participant timeline and follow-ups

Recruitment, informed consent, eligibility screening, randomisation, baseline assessment, intervention and follow-ups will all be automated and computerised. Two email reminders will be sent 1 week apart. Follow-up at 2 months after randomisation will be initiated by sending an email with a hyperlink to a web-based questionnaire. Non-responders to follow-up will receive up to three follow-up email reminders. A study timeline is presented in figure 3. Note that this is the first ever effectiveness study of a brief digital intervention for procrastination of its kind, and as such we have no previous studies to guide us on how long intervention effects may persist. We took a pragmatic approach and decided to keep the follow-up interval short enough to stay within the same academic semester, but still enough removed from the intervention itself to decide if there were any lasting effects.

**Figure 3 F3:**
[figure not shown]
SPIRIT figure presenting participant timeline. SPIRIT, Standard Protocol Items: Recommendations for Interventional Trials.

### Assignment of interventions

Participants will be randomised using block randomisation (with random block sizes of 2 and 4). The randomisation sequence will be computer generated, and neither research personnel nor participants will be able to manipulate the sequence. As all study procedures are automated, thus randomisation cannot be subverted.

### Sample size

The data collected in this trial will be analysed using Bayesian analysis,^33^ which delivers a posterior probability of effect regardless of the number of participants included. We will not use null hypothesis testing; therefore, a traditional power calculation is not required to determine the required sample size to control type I and II errors. Instead, we conducted a Monte Carlo simulation study, assuming a standardised effect of 0.35 Cohen’s d of the intervention on the primary outcome (procrastination behaviour). To at least 80% of the time estimate a posterior probability of effect of at least 95%, the Monte Carlo simulations indicated that data from 1000 participants are required for analysis, meaning that 2000 participants are required to be randomised when assuming a 50% attrition rate. Note that this intervention and trial is novel, and as such there are no previous studies to rely on the determination of effect size. However, a previous study comparing guided and unguided self-help using iCBT with a wait-list control observed effects sizes ranging from 0.5 to 0.7 Cohen’s d.^14^ We anticipate that our brief intervention will be less effective than a full therapy programme, and we have thus assumed a small to medium Cohen’s d of 0.35.

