## Discussion

This RCT aims to estimate the effects of a brief digital procrastination intervention on procrastination behaviours among university students in Sweden. It will add findings on how to support students to overcome procrastination—something that is inadequately evaluated. This is so despite procrastination behaviours being common among university students, and known to cause ill health, distress and negatively impact academic performance.^3 5^ Digital interventions could fulfil these needs and are scalable to a large group of individuals at a low cost. The low cost of delivering digital interventions,^35^ and the low participant burden of completing a brief screening questionnaire, justifies even small effects from the intervention.

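### The 1000 analysed participants do not follow from the stated inputs: d = 0.35 with the 80%/95% criterion needs about 202, and 1000 gives 80% at d of about 0.16

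*Protocol article*

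**What the plan says.** The Sample size section of the protocol article gives the inputs and the result together.

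- Effect: "assuming a standardised effect of 0.35 Cohen’s d of the intervention on the primary outcome" (procrastination behaviour, measured by the PPS).
- Criterion: "To at least 80% of the time estimate a posterior probability of effect of at least 95" per cent.
- Result: "the Monte Carlo simulations indicated that data from 1000 participants are required for analysis".
- Inflation: "2000 participants are required to be randomised when assuming a 50% attrition rate".

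The section then defends 0.35 as a deliberate choice, set below the 0.5 to 0.7 seen with a fuller therapy programme. The abstract repeats the inputs and the result ("indicated that data from 1000 participants are required for analysis").

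The design is "A two-arm, parallel groups (1:1), single-blind randomised controlled trial", and the Assignment of interventions section states: "Participants will be randomised using block randomisation (with random block sizes of 2 and 4" participants. Allocation is therefore by individual. The Data analysis section specifies a linear model on the standardised PPS, adjusted for age, gender and baseline PPS, with a varying intercept for each university. Its Student-t priors have 3 df and scale 2.5.

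**The concern.** A standardised difference of 0.35 is not small in sample-size terms, and an 80% chance of passing a 95% posterior threshold is not a strict criterion. One thousand analysed participants is several times what a statistician would expect from that pair.

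The calculation is the only justification given for randomising 2000 students, and it is the article's only statement of what the trial can detect. If the number and its inputs do not belong together, the reader is told the wrong design sensitivity. On the stated inputs, about 2000 − 404 = 1596 of the planned students are also unexplained.

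**Working it through.** **Inputs.** d = 0.35 with SD 1, threshold 95%, success probability 80%, 1000 analysed, 50% attrition (Sample size). Allocation 1:1 by individual (Methods and analysis; Assignment of interventions). Weak priors and a university intercept (Data analysis).

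**The plan's own figures.** The attrition step reproduces: 1000 / (1 − 0.5) = 2000. The 1000 does not, as follows.

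**Closed form.** The outcome is standardised, so a prior of scale 2.5 is very wide next to an effect of 0.35. The posterior probability then reaches 95% almost exactly when the estimate exceeds 1.645 standard errors.

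- Number needed per arm: 2 × (1.645 + 0.842)² / 0.35² = 100.9, so 101 per arm and 202 in total. Randomised: 202 / 0.5 = 404.
- Probability of success with 1000 analysed at d = 0.35: Φ(0.35 × √1000 / 2 − 1.645) = Φ(5.534 − 1.645) = 0.99995.
- Effect giving 80% with 1000 analysed: 2 × (1.645 + 0.842) / √1000 = 0.157.
- Ratio of stated to derived number: 1000 / 202 = 4.95.

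**Simulation of the posterior criterion** (normal likelihood, 4000 replicates, d = 0.35):

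| Analysed | Student-t(3, scale 2.5) prior | N(0,1) prior |
|---|---|---|
| 200 | 0.794 | 0.792 |
| 202 | 0.808 | 0.794 |
| 210 | 0.810 | 0.806 |
| 1000 | 1.000 | 1.000 |

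The simulation standard error near 0.80 is √(0.8 × 0.2 / 4000) = 0.006, so this agrees with the closed form under either prior.

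**Could a feature of the design close the gap?**

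- *University intercept.* Allocation is within universities, so there is no cluster design effect. A simulation with university effects (assumed: 10 universities, intraclass correlation 0.05, no baseline correlation; effects fitted as fixed) gave 0.801 at 202 analysed. Reaching 1000 would need a variance inflation of 4.95.
- *Baseline adjustment.* If 0.35 is scaled to the marginal SD, adjustment lowers the number needed. If it is scaled to the residual SD, adjustment leaves it unchanged. In neither case does it raise it.
- *A sceptical prior.* With a normal prior of SD τ and standard error s = 2/√1000 = 0.0632, the success probability is Φ(0.35/s − 1.645 × √(1 + s²/τ²)). At τ = 0.025 this is 0.855, and at τ = 0.02 it is 0.531. A prior SD near 0.025 would be needed, and none is described.
- *A stricter criterion.* A 97.5% threshold with 80% success needs 258. The same threshold with 99% success needs 600.

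**Unstated inputs that come near 1000.** With d = 0.175 (half the stated value), the number is 808 at the 95% threshold and 1026 at 97.5%. For an interaction of 0.35 with an evenly split binary covariate, it is 4 × 202 = 808 or 4 × 258 = 1032. Neither is mentioned, and the text ties 1000 to 0.35 on the primary outcome.

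**The case against.** The strongest reply is that the criterion is a minimum, and 1000 analysed participants meet it with room to spare. The trial is not underpowered for 0.35, and neither the estimand, the analysis nor recruitment changes. All of this stands, and it makes the matter one of correcting a stated figure. It does not rescue the wording: both places say 1000 are *required*, which is out by a factor of about five.

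A second reply is that an article condenses a fuller protocol. That would excuse a missing detail. Here the inputs and the output are both printed, and they are incompatible.

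Three stronger readings are tempting, and the document does not support them.

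- A reader might infer that a posterior probability below 95% will be taken as 80% assurance against an effect near 0.35. But the protocol disclaims null hypothesis testing, sets no 95% decision rule for the analysis, and reports posterior medians with 95% compatibility intervals. Those intervals will show the precision actually achieved, whatever effect was assumed at design.
- A reader might take the Discussion's remark that low cost and burden "justifies even small effects from the intervention" as a sign that the real target was about 0.16. That remark concerns what is worth delivering. It is not a design target, and the Sample size section argues explicitly for 0.35.
- A reader might quote still smaller numbers or effects after baseline adjustment. Those depend on an assumed correlation and on which SD scales d, and the article gives neither.

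It is also fair to note that the Data analysis section does not expressly name the prior on the treatment coefficient. The Student-t prior is given for covariate coefficients, and standard normal priors appear in the sentence on university intercepts. The result is the same under both.

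**Conclusion.** The stated sample size does not follow from its stated inputs. They give about 202 analysed and 404 randomised, against 1000 and 2000. With 1000 analysed, the stated criterion is met with probability above 99.9% at d = 0.35. The effect met with about 80% probability is d of about 0.16.

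These figures are unadjusted. They assume equal arms, individual randomisation and a prior on the treatment effect that is weak on the SD scale. They do not depend on any assumed baseline correlation.

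It would go too far to conclude that the effect size is the wrong element and the 1000 is right, or the reverse. The document alone cannot show whether d, the number or an unreported simulation input is misstated.

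**What to change.** Check or re-run the simulation, then reconcile the effect size, the criterion and the number in the Sample size section and the abstract.

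- If an input not reported in the article produced 1000 (a smaller d, a stricter threshold, an interaction target), state it in place of the present inputs.
- If not, keep the 2000 target, remove the claim that 1000 are required for d = 0.35, and say what 1000 analysed participants deliver. For example: *with 1000 analysed, the chance of reaching the 95% posterior threshold exceeds 99.9% at d = 0.35 and is about 80% at d of about 0.16, before covariate adjustment.*

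Figures that rest on an assumed baseline correlation should stay out of the protocol text. The cost is one simulation run and a rewording in two places, with no change to recruitment, outcomes or analysis.
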